### Work package 6:

#### *Objective 6: Validation of a new model, based on grey scale ultrasound and colour Doppler information, specifically designed for difficult tumours.*

The aim is to validate a logistic regression model, based on grey scale ultrasound and colour Doppler, specifically designed for difficult tumours. The main question is: “Can unnecessary exploratory laparotomies be avoided in a number of cases?” Study participants in the prospective set will be offered in a randomised way the standard hospital approaches or standard hospital approaches + the model result. This work package is further subdivided in 2 tasks:

### Task 6.1: Data collection

At least 2,000 new patients with persisting adnexal tumours will be examined. This results in a collection of roughly 300 difficult masses. The hypothesis is that adding the prediction by the model, developed for this specific subgroup of tumours, to the decision tree allows a significant reduction in the number of exploratory laparotomies for benign tumours when compared to the standard hospital procedure. Therefore, cases where the clinicians state to be uncertain about the diagnosis, will be randomised in two arms in 1:2 ratios:

- arm (A): standard hospital procedure approach
- arm (B): standard hospital procedure approach + result of difficult tumours model.

So, we will have roughly 100 cases in the control arm (arm A) and 200 cases in the model arm (arm B).

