#### **O6: Validation of a new model, based on grey scale ultrasound and colour Doppler information, specifically designed for “difficult” tumours**

Using subjective evaluation of grey scale and Doppler ultrasound findings, an experienced ultrasound examiner using a good ultrasound system can correctly classify ovarian tumours as benign or malignant in most cases. The experts reached in IOTA 1 and IOTA 1b a sensitivity of 88% (234/266) and 90% (129/143), respectively, and a specificity of 95% (762/800) and 93% (338/364) ([44], unpublished data). In 8% of the cases, the ultrasound examiner found it difficult to discriminate between benign and malignant tumours (90/1066 in IOTA 1, 39/507 in IOTA 1b) [45]. Borderline tumours were over-represented among these “uncertain” masses, being three times more common among the “uncertain” masses than among the other ones. Of those borderline tumours, 60% (33/55) were correctly classified (i.e., classified as malignant) by the expert, compared to 95% (762/800) of the benign tumours, 96% (162/169) of the primary invasive tumours and 93% (39/42) of the metastatic tumours [45]. A logistic regression model has been constructed using data of the 54 “uncertain” cases with papillary projections in IOTA 1, but its performance was not stable: the area under the ROC curve was 0.88 on the development set, but dropped to 0.73 on an independent test set. Combining all data available in IOTA 1, 1b and 2 (IOTA 2 data collection just recently closed), we now have full preoperative information of 3,500 tumours including 250 cases which were difficult to preoperatively predict according to the investigators. Moreover, tumours for which the output of the main logistic regression is close to the decision boundary can also be regarded as difficult to classify. Using all available grey scale ultrasound and colour Doppler data of difficult tumours in IOTA 1, 1b and 2, a logistic regression model has specifically been developed for these difficult masses, with an area under the ROC curve of 0.85 on both development and test set (unpublished data).

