### **Task 1.5: Patient selection for Second stage tests**

The IOTA 2 dataset enables us to describe the population characteristics of each centre in correlation with the performance of the models in that centre. This gives us the opportunity to define centre-specific cut-offs above which an adnexal mass is classified as malignant. Whenever the probability of malignancy is amongst the 15% that lies close to the decision boundary of LR1, the examiner will be obliged to perform one of the second stage tests. In this way, we expect that the adnexal masses of approximately 300 patients will be classified as “difficult” and will need a second stage test.

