### Task 6.2: Validation of the model

In both arms, the sensitivity and specificity will be calculated and compared. An increase of 10% specificity in the model arm (arm B), at an equivalent sensitivity in arm A and B, will be regarded as clinically relevant.

This analysis will be performed twice: 1) overall and 2) stratified by the degree of expertise of the ultrasound examiner. The 2nd analysis is planned due to the fact that less experienced ultrasound examiners might benefit more from the use of such model for difficult tumours than highly experienced investigators.

|                                        |
|----------------------------------------|
| Expertise in supporting centres |
|----------------------------------------|

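### Task 6.1 expects 100 versus 200 randomised cases, a count that matches the 15% LR1 band, but it randomises only clinician-uncertain cases, which the protocol's own rates put at about 143 to 200 in total

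*Protocol*

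**What the plan says.** Task 6.1 (Work package 6) starts from the recruitment target: "At least 2,000 new patients with persisting adnexal tumours will be examined". It continues: "This results in a collection of roughly 300 difficult masses". It then sets the randomisation rule, "cases where the clinicians state to be uncertain about the diagnosis, will be randomised in two arms in 1:2 ratios", and draws the arm sizes from it: "So, we will have roughly 100 cases in the control arm (arm A) and 200 cases in the model arm (arm B".

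The count of 300 also appears in Task 1.5, the rule for sending a mass to second-stage testing. The trigger there is a model output: "Whenever the probability of malignancy is amongst the 15% that lies close to the decision boundary of LR1". Task 1.5 gives its yield as "we expect that the adnexal masses of approximately 300 patients will be classified as" difficult.

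The introduction to Work package 1 uses a third definition, under which a mass counts as difficult if either the subjective assessment or the model prediction is uncertain.

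For examiner uncertainty alone, the consortium background for O6 reports that "the ultrasound examiner found it difficult to discriminate between benign and malignant tumours (90/1066 in IOTA 1, 39/507 in IOTA 1b". The same section gives 250 such cases among 3,500 tumours over IOTA 1, 1b and 2. The consortium background for O1 puts the share at about 8%. The literature background for O6 says that an experienced examiner will lack a confident and correct diagnosis in about 1 case in 10.

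Task 6.2 sets the benchmark for the comparison: "An increase of 10% specificity in the model arm (arm B), at an equivalent sensitivity in arm A and B" is to count as clinically relevant.

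**The concern.** The arm sizes are presented as the consequence of the randomisation rule, but the count behind them belongs to a different rule. Being near the LR1 boundary and being called uncertain by the examiner are separate conditions. The consortium background for O6 keeps them apart when it says that masses near the model boundary can also be regarded as difficult.

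Work package 6 is the only package with a randomised comparison. Tasks 2.2, 4.2 and 5.2 rely on matched historical controls. If Task 6.1 is followed as written, that comparison will be smaller than stated, and Task 6.2 then repeats it by examiner expertise. A shortfall that comes from the eligibility rule cannot be repaired once recruitment has ended.

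**Working it through.** **Inputs from the protocol.** N = 2,000 patients and 1:2 allocation (Task 6.1); 15% LR1 band (Task 1.5); 90/1,066, 39/507 and 250/3,500 (consortium background, O6); about 8% (consortium background, O1); about 1 in 10 (literature background, O6).

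**Step 1: reproduce the stated figure.** Randomised = N × eligible share; arm A is one third, arm B two thirds.
- 2,000 × 0.15 = 300; 300/3 = 100; 2 × 300/3 = 200. This matches Task 6.1 exactly.

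**Step 2: apply the rule that Task 6.1 states.** The pooled rate is (90 + 39)/(1,066 + 507) = 129/1,573 = 8.2%.

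| Source of rate | Rate | Randomised of 2,000 | Arm A / Arm B |
|---|---|---|---|
| IOTA 1, 1b and 2: 250/3,500 | 7.1% | 143 | 48 / 95 |
| IOTA 1b: 39/507 | 7.7% | 154 | 51 / 103 |
| Consortium background, O1 | 8% | 160 | 53 / 107 |
| IOTA 1 and 1b pooled: 129/1,573 | 8.2% | 164 | 55 / 109 |
| IOTA 1: 90/1,066 | 8.4% | 169 | 56 / 113 |
| Literature background, O6 | 10% | 200 | 67 / 133 |

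At the pooled rate the shortfall is (300 − 164)/300 = 45%; at the most favourable rate it is (300 − 200)/300 = 33%.

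**Step 3: enrolment needed for 300 under the stated rule.** 300/0.0820 = about 3,660 patients; 300/0.0714 = 4,200; 300/0.10 = 3,000.

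**Step 4: yield of the either/or rule of Work package 1.** With 300 masses in the band and 164 examiner-uncertain, the union runs from 300 (every uncertain mass lies in the band) to 300 + 164 = 464 (no overlap). The protocol does not give the overlap.

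**Step 5: consequence, for illustration only.** The protocol gives no benign share, control specificity, significance level or power for this package. I assume 65% benign, specificity 60% versus 70% (reading the 10% as points), two-sided 5%, and a two-proportion test with pooled variance under the null.
- At 100/200, the benign masses number 65 and 130, and power is 29%.
- At 54.7/109.3, they number 35.5 and 71.1, and power is 18%.
- Raising control specificity from 60% to 80% moves these to 29–49% and 18–31%. Varying the benign share over 50–75% and control specificity over 50–80% gives 21–54% and 14–35%.
- The 95% CI half-width for the specificity difference is 1.96 × √[p(1 − p)(1/nA + 1/nB)] with p = 0.65. At the stated arms it is 1.96 × √[0.2275 × (1/65 + 1/130)] = 14 points. At 55/109 it is 1.96 × √[0.2275 × (1/35.5 + 1/71.1)] = 19 points.

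**The case against.** Three arguments can be made for the protocol.

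- **Task 6.1 never cites the LR1 band.** It may use clinician uncertainty as loose shorthand for all difficult masses. In that case the trigger is badly worded and the sample is not lost. This is a possible intention, but the literal text limits randomisation to stated clinician uncertainty, and no other derivation of 300 is given. On either reading the text has to change.
- **Earlier uncertainty rates may not carry over.** In IOTA phase 3 the examiner sees the main model's prediction straight after the scan, and Task 6.1 does not say whether uncertainty is judged before or after that. Task 1.2 freezes the certainty rating before the model output appears, which favours the earlier rates, but the point stands as a reason for a range. A higher rate among less experienced examiners is not supported: the all-phase figure, which includes the phase 2 centres with varied experience, is the lower one (7.1% against 8.2%).
- **Work package 6 is one of six.** The 2,000-patient target and the Work package 1 validation are untouched. This is correct and limits the reach of the point.

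A reader might also infer that a non-significant difference in sensitivity will be taken as equivalence. Task 6.2 names no test and says nothing of the kind, and a margin may be set in a statistical analysis plan that is not at hand. No point is made of it here.

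**Conclusion.** The stated arms of 100 and 200 do not follow from the stated randomisation rule. On the protocol's own rates, 2,000 patients give about 143 to 200 randomised cases, or 48/95 to 67/133, with 55/109 at the pooled 8.2%. This assumes that earlier uncertainty rates carry over and that every uncertain case is randomised.

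Two stronger readings go too far. One is that the arms will hold exactly 55 and 109; that is an expectation at one of several documented rates. The other is that the mismatch spoils an otherwise well-powered comparison. The protocol states no power target for this package. At an assumed 65% benign and control specificity of 60–80%, power for a 10-point gain stays below 50% even with 300 cases. The mismatch makes a weak comparison weaker. The count discrepancy does not depend on those assumptions; the power and interval figures do.

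**What to change.** Give one reconciled definition of a difficult mass across the introduction to Work package 1, Task 1.5 and Task 6.1, and say whether uncertainty is judged before or after the examiner sees the model output. Then take one of two routes:

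1. **Keep randomisation to clinician-uncertain cases.** Restate the expected arms as about 55 and 109 (range 48/95 to 67/133), and acknowledge the lower precision for the 10-point specificity criterion.
2. **Randomise on the either/or rule of Work package 1.** State that this yields about 300 to 464 cases depending on overlap, and that it brings in masses about which the examiner was confident. A reader might take this route as simply restoring the 300. It does so only if every uncertain mass lies inside the band. It also changes the population compared, so a larger count need not bring back the same power.

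The choice is the sponsor's. Either route is a short amendment with no extra enrolment. Keeping both the present rule and the target of 300 would instead need about 3,660 patients at 8.2% (3,000 to 4,200 over the documented rates).

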### Task 6.2: Validation of the model

In both arms, the sensitivity and specificity will be calculated and compared. An increase of 10% specificity in the model arm (arm B), at an equivalent sensitivity in arm A and B, will be regarded as clinically relevant.

This analysis will be performed twice: 1) overall and 2) stratified by the degree of expertise of the ultrasound examiner. The 2nd analysis is planned due to the fact that less experienced ultrasound examiners might benefit more from the use of such model for difficult tumours than highly experienced investigators.

|                                        |
|----------------------------------------|
| Expertise in supporting centres |
|----------------------------------------|

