### **6. Subjective assessment**

After ultrasonographic examination of the mass the investigator gives his subjective assessment of the mass:

A: Malignant (1) or benign (0)?

B: Probability of malignancy:  
(=level of certainty)

|                        |
|------------------------|
| 1 = benign             |
| 2 = probably benign    |
| 3 = uncertain          |
| 4 = probably malignant |
| 5 = malignant          |

C: Self impression: presumed histological diagnosis (e.g. dermoid, serous cystadenoma, endometrioma...)

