#### **Task 1.2: Data collection and management**

For the data collection of IOTA phase 1 and IOTA phase 2, a dedicated, secure data collection system was developed. A unique identifier was generated automatically for each patient's record based on the identifier for the centre, the patient's birthday and the date of the ultrasound scan. Clinicians at each centre could only view or update patients records from their own centre. In IOTA phase 1, the data collection was performed web-based, the investigators needed to login and to complete online a case report form. Data security was ensured by not recording the patient's name and by encrypting all data communication using a 54-bit SSL (Secure Socket Layer) certificate. For IOTA phase 2, an Astraia software application has been developed ([www.astraia.com](http://www.astraia.com)) which enables the researchers to complete the data offline in an electronical case report form. And afterwards, they transferred it to a central database located in Belgium. Since this second method was approved much more user-friendly by the clinicians, the data collection of IOTA phase 3 will be similarly executed.

Each participating centre inserts the clinical and ultrasound data in a specifically designed Astraia study screen. No missings are allowed during data submission, except for the CA-125 marker. A subjective assessment whether the tumour seems benign or malignant as well as the degree of certainty is given by the ultrasound examiner and this assessment is frozen in the local Astraia database before the results of the mathematical model become available to the examiner.

### VARIABLES needed to test mathematical models in IOTA PHASE 3

| Variable                          | Acronym        | LR | BMLP | BPER | LS-SVM/
RVM | MC1 | MC2 |
|-----------------------------------|----------------|----|------|------|----------------|-----|-----|
| Personal history of ov. cancer    | Pershistovca   | X  | X    | X    | X              | X   | X   |
| Current use of hormonal therapy   | Hormtherapy    | X  | X    |      | X              |     |     |
| Age                               | Age            | X  | X    | X    | X              | X   | X   |
| Diameters of the lesion           | LesD1-3        | X  | X    | X    |                | X   | X   |
| Pain during examination           | Pain           | X  | X    |      |                |     |     |

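### Work package 6 leaves the frozen pre-model benign/malignant call out of both planned arm comparisons; adjusting for it would improve precision, though its absence is not an error

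*Protocol*

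**What the plan says.** Task 6.1 describes the randomised set: "cases where the clinicians state to be uncertain about the diagnosis, will be randomised in two arms in 1:2 ratios", to the standard hospital approach (arm A) or the same approach plus the difficult-tumours model result (arm B). On numbers it says "This results in a collection of roughly 300 difficult masses", split into roughly 100 in arm A and 200 in arm B.

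Task 6.2 gives the analysis: "In both arms, the sensitivity and specificity will be calculated and compared". It then sets the size of benefit that would matter: "An increase of 10% specificity in the model arm (arm B), at an equivalent sensitivity in arm A and B, will be regarded as clinically". Two analyses are listed: "This analysis will be performed twice: 1) overall and 2) stratified by the degree of expertise of the ultrasound examiner". No test, model or covariate is named, either there or in section 10 (Statistical analysis).

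Two other sections describe a baseline measurement. Section 6 says "After ultrasonographic examination of the mass the investigator gives his subjective assessment of the mass": a forced malignant/benign choice, a five-level certainty scale and a presumed histology. Task 1.2 adds that "this assessment is frozen in the local Astraia database before the results of the mathematical model become available to the examiner" and allows no missing values at submission apart from CA-125.

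**The concern.** For every randomised mass the trial already holds a benign/malignant call made without knowledge of the model. A mass misjudged at that point may well be misjudged later too. If so, part of the between-mass variance in the work package 6 outcome is predictable from data in the database. Task 6.2 names one stratifier, examiner expertise, and does not name this one.

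The contrasts are small. Only benign masses inform specificity and only malignant masses inform sensitivity, so each uses a fraction of 100 v 200. With arms of that size, a chance difference between arms in how many masses were already called correctly adds noise to the estimated effect of the model. Adjustment removes that noise to the extent that the frozen call predicts the final classification.

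**Working it through.** **The plan's own figure.** Task 1.5 uses 15% of masses near the LR1 decision boundary: 2,000 × 0.15 = 300. Split 1:2, this is 100 and 200, which matches Task 6.1. No power, significance level or control-arm specificity is stated for work package 6, so there is no power figure to reproduce.

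**Inputs.** From the protocol: 100 v 200 masses and a gain of 10 points in specificity, read as absolute. Assumed, because the documents do not give them: 60% of randomised masses are benign (60 v 120), specificity is 60% in arm A and 70% in arm B, and the test is two-sided at 5%. Also assumed is ρ, the correlation among benign masses between a correct frozen call and a correct final classification.

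**Unadjusted.** SE = √(0.60×0.40/60 + 0.70×0.30/120) = √(0.00400 + 0.00175) = 0.0758. Then 0.10/0.0758 = 1.32, and power = Φ(1.32 − 1.96) ≈ 26%.

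**Adjusted.** Adjustment multiplies the variance by about (1 − ρ²).

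| ρ | 1 − ρ² | SE | 0.10/SE | Power |
|---|---|---|---|---|
| 0 | 1.00 | 0.0758 | 1.32 | 26% |
| 0.3 | 0.91 | 0.0723 | 1.38 | 28% |
| 0.5 | 0.75 | 0.0657 | 1.52 | 33% |
| 0.7 | 0.51 | 0.0542 | 1.85 | 46% |

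A simulation of this case, using linear adjustment with an arm-by-baseline term and robust standard errors, gave 25% v 32% at ρ = 0.5 and 24% v 42% at ρ = 0.7. The last row of the table is therefore somewhat optimistic for that estimator.

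**Second case, different method.** With 65 v 130 benign masses and 70% v 80%, 8,000 simulated trials of a Mantel-Haenszel risk difference stratified by the frozen call gave about 34% power unadjusted. With stratification power was 37%, 44% and 58% at ρ = 0.3, 0.5 and 0.7. Type I error stayed near 5%, the 10-point difference was recovered unchanged, and there was no material loss at ρ = 0.

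**Range.** Let the benign share run from 50% to 75% and arm A specificity from 50% to 85%. Unadjusted power (pooled-variance formula) then runs from 21% to 70%, and ρ = 0.5 adds about 6 to 11 points.

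**Ceiling on ρ.** Two binary variables with different success rates cannot be perfectly correlated. If the frozen call is as specific as arm A, the largest ρ in arm B is √[pA(1 − pB)/((1 − pA)pB)]:
- 60% v 70%: √(0.6×0.3/(0.4×0.7)) = 0.80
- 80% v 90%: √(0.8×0.1/(0.2×0.9)) = 0.67

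So ρ = 0.7 is possible in the first case and impossible in the second.

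**Smaller randomised set.** Task 6.1 randomises masses about which the clinician is uncertain, and the state-of-the-art text for O6 puts these at 8% in earlier phases: 2,000 × 0.08 = 160. With 65% benign and 70% v 80%, power is then 21% unadjusted, 27% at ρ = 0.5 and 36% at ρ = 0.7.

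**The case against.** The strongest reply is that Task 6.2 is silent and has not decided anything. It never says the comparison is unadjusted, and covariates are commonly left to a statistical analysis plan, which is not at hand. Comparing proportions between randomised arms is unbiased, and its ordinary standard error already covers chance imbalance. All of this stands. A reader might infer that the protocol has chosen a raw analysis and made a mistake, but the text does not support that. What remains is narrower: Task 6.2 lists its two analyses and the stratifier for one of them, and a complete baseline call is in neither.

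A reader might also take the frozen call to be a baseline value of the same outcome. That is true only if the outcome is a revised diagnosis. The hypothesis in Task 6.1 concerns exploratory laparotomies for benign tumours, while Task 6.2 speaks of sensitivity and specificity and does not say which decision counts as positive. If laparotomy is analysed, the frozen call is a predictor and not the same measure, though it remains a valid covariate.

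The size of the gain is open to doubt as well. The main model's prediction, the second-stage tests and, in arm B, the difficult-tumours model all come after the frozen call and are meant to change uncertain judgements, which may lower ρ. A gain as large as 28 points might be inferred from ρ = 0.7 at 80% v 90% with 70 v 140 benign masses. That needs a correlation above the 0.67 ceiling, if the frozen call is as specific as arm A.

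Finally, the certainty level adds little: entry requires the clinician to be uncertain, so it is nearly constant in the randomised set.

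**Conclusion.** The point holds as an efficiency improvement. A complete binary call that precedes the model result is available, neither analysis in Task 6.2 uses it, and adjusting for it keeps the type I error near 5% at practically no cost in precision.

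In the 60 v 120, 60% v 70% case the gain is about 2 points of power at ρ = 0.3, 7 at 0.5 and at most about 20 at 0.7. It rests on an assumed benign share, arm A specificity and significance level, and above all on a correlation that the documents do not give. The same factor (1 − ρ²) applies to the variance of the sensitivity contrast, with ρ taken among malignant masses. Adjustment leaves this case well short of 80% power, so it does not replace a sample-size justification.

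**What to change.** In Task 6.2:

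- Name the post-allocation decision that is classified as positive or negative, a revised diagnosis or exploratory laparotomy, and reconcile this with the hypothesis in Task 6.1.
- Estimate the arm difference in specificity among benign masses, and in sensitivity among malignant masses, adjusted for or stratified by the frozen binary call. Report a covariate-standardised risk difference with a robust confidence interval, beside the raw proportions.
- Use the same adjustment in the expertise-stratified analysis.
- Leave the certainty level out of the required adjustment.

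The adjustment costs a short paragraph and a few lines of code, with no extra patients and no new baseline data. Naming the outcome may cost slightly more: no section describes recording a second examiner diagnosis after allocation, so if that is the outcome chosen, a field for it may have to be added.

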### 3. Design

#### Number of patients / tumours

2,000 patients with at least one histologically examined adnexal mass will be recruited for the third part of the IOTA trial (i.e. the prospective testing of new mathematical models and second stage tests).

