#### Outcome measures

The histological classification of removed tissue and the findings at surgery.

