## Exclusion criteria

- Patients with more than one lesion in the same ovary or in two different ovaries will be included in the data collection, but in case of two different non-physiological conditions (based on the pathology report) the results will be excluded from the main analysis of the data. The reason for this approach is to avoid several difficulties: e.g. to assess the Doppler signals of different masses separately, and to know the contribution of each mass in particular elevation of serum CA 125 levels).
- Pregnancy is not an exclusion criterium, but the data from pregnant patients are analysed separately, because the physiology is different (e.g. different colour Doppler findings and higher serum CA 125 levels).
- Preferably surgery is scheduled within one week after ultrasonography. If more than 90 days have passed before the patient has been operated upon, the patient is excluded for analysis, except if a new scan has been performed prior to surgery.

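### Work package 6 hypothesises fewer exploratory laparotomies for benign tumours, but Task 6.2 compares only sensitivity and specificity, and randomised women who have no surgery leave that comparison

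*Protocol*

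**What the plan says.** Work package 6 puts its main question as "Can unnecessary exploratory laparotomies be avoided in a number of cases". Task 6.1 turns this into a hypothesis: adding the model's prediction "allows a significant reduction in the number of exploratory laparotomies for benign tumours when compared to the standard hospital procedure". The randomisation follows from that hypothesis: "cases where the clinicians state to be uncertain about the diagnosis, will be randomised in two arms in 1:2 ratios", giving about 100 women under standard procedure (arm A) and 200 with the model result added (arm B).

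Task 6.2 then specifies the analysis: "In both arms, the sensitivity and specificity will be calculated and compared". Its threshold of clinical relevance is on the same scale, and the sentence that sets it opens with the words "An increase of 10% specificity in the model arm (arm B), at an equivalent sensitivity in arm A and B, will be regarded as clinically". Laparotomies are not mentioned in Task 6.2.

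Four other places bear on this:

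- Section 3, Outcome measures: "The histological classification of removed tissue and the findings at surgery". Surgical route is not named.
- Section 3, Number of patients / tumours: "2,000 patients with at least one histologically examined adnexal mass will be recruited".
- Section 4, Exclusion criteria: "If more than 90 days have passed before the patient has been operated upon, the patient is excluded for analysis", with an exception for women rescanned before a later operation.
- Section 8, Surgical investigation: the choice between laparoscopy and open surgery rests with the surgeon, and cytology or needle biopsy does not count as histological classification.

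**The concern.** The hypothesis is about what was done to women with benign tumours. The analysis is about how their masses were labelled. The two coincide only if the label determines the operation, and Section 8 says that it does not. The protocol's only randomised comparison could therefore report a specificity gain without showing that any laparotomy was avoided, or miss laparotomies that were avoided.

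There is also a selection problem. Women are randomised at the point of diagnostic uncertainty, before surgery. Sensitivity and specificity need histology, and no follow-up reference standard is given for women who are not operated on. Whether a randomised woman is analysed thus depends on a later decision that the model result may influence. If non-operation differs by arm, randomisation no longer fully protects the comparison.

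This is not detail left to a statistical analysis plan, because Task 6.2 itself fixes both the comparison and its threshold.

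**Working it through.** **Arm sizes.** Task 1.5 expects 15% of masses to be difficult: 2,000 × 0.15 = 300. At 1:2 this gives 300/3 = 100 and 200, as in Task 6.1. Work package 6 states no alpha, power, baseline specificity or laparotomy rate, so the rates below are assumptions.

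**Step 1: how well specificity stands in for laparotomy.** Let L1 and L0 be the laparotomy rates in benign masses called malignant and called benign, taken as equal in both arms. With specificity s, the laparotomy rate among benign masses is (1 − s) × L1 + s × L0. A 10-point gain in s changes it by −0.10 × (L1 − L0).

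- L1 = 100%, L0 = 0%: a fall of 10 points.
- L1 = 70%, L0 = 20%: a fall of 5 points.
- L1 = 50%, L0 = 40%: a fall of 1 point.

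The proxy is exact only if every malignant call and no benign call leads to laparotomy.

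**Step 2: effect of losing women without histology.** Assume 65% benign (65 in arm A, 130 in arm B), true specificity 50% and 60%, and surgery for every mass called malignant. Arm A has 32.5 true negatives and 32.5 false positives. Arm B has 78 true negatives and 52 false positives. Of the 78, 65 would be called benign under standard care and 13 are newly reclassified. Observed specificity = retained true negatives / (retained true negatives + false positives).

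With 15% of masses called benign unoperated in arm A: 32.5 × 0.85 = 27.6, and 27.6/60.1 = 45.9%. In arm B, 15% of the 65 also go unoperated, leaving 55.25. The 13 are varied:

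| Share of the 13 unoperated | Arm B observed | Observed gain |
|---|---|---|
| 15% | 66.3/118.3 = 56.0% | 10.1 points |
| 30% | 64.35/116.35 = 55.3% | 9.4 points |
| 100% | 55.25/107.25 = 51.5% | 5.6 points |

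Other assumed rates widen the range. If a share f of true negatives is lost, observed specificity is s(1 − f)/[s(1 − f) + 1 − s].

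- Equal f of 10–40% in both arms, with arm A specificity of 50–80%: observed gain 9.9 to 13.8 points, so roughly kept or overstated.
- Loss in arm B only, true 70% versus 80%: f = 20% gives 0.64/0.84 = 76.2%, a gain of 6.2 points; f = 40% gives 0.48/0.68 = 70.6%, a gain of 0.6 points.

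**Step 3: precision of a laparotomy endpoint.** For two proportions at 100 versus 200, two-sided 5%, with the pooled variance under the null, power for a 10-point fall is 49% from 30%, 41% from 40% and 38% from 50%. For 80% power, arm A would need 216, 265 or 290 women, with twice as many in arm B.

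These are falls among all randomised women. At 65% benign, a 10-point fall confined to benign masses is 0.65 × 10 = 6.5 points on that scale. From 0.65 × 50% = 32.5% to 0.65 × 40% = 26%, the same formula gives about 22% power. The planned specificity comparison, 50% versus 60% in 65 and 130 benign masses, has about 26%.

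**The case against.** The strongest defence is that specificity is the intended measure of avoided laparotomy. Task 5.2, on 3D ultrasound, explicitly links higher specificity to fewer unnecessary laparotomies, and Task 6.2 sets its threshold on that scale. This stands as far as it goes. A reader might infer that the hypothesis is never tested. The protocol does not support that: it is tested indirectly, through a proxy that Section 8 leaves loose.

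A second defence is that avoiding laparotomy is not the same as avoiding surgery. The Rationale says that most benign non-functional tumours can be handled by laparoscopy or a low transverse incision, and Section 8 treats a persistent mass as an indication for surgery. A woman moved from laparotomy to laparoscopy keeps her histology and stays in the analysis. Non-operation may also be uncommon here. The follow-up option in Section 8 concerns small smooth unilocular cysts, whereas 54 of the 90 uncertain masses in the first IOTA phase (60%) had papillary projections, which make the wall irregular by the protocol's definition. This limits the selection problem without removing it: the background sections foresee both conservative treatment and operations that might prove unnecessary. It does not touch the endpoint mismatch, since laparotomies are not compared even if every woman is operated on.

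It is also fair that the 90-day rule does not remove everyone operated on late, since rescanned women stay in, and that the electronic form is not shown and may already hold the surgical route.

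**Conclusion.** The point holds in two parts. First, the hypothesis and the planned analysis concern different quantities. This follows from the text and needs no assumption. Under the assumed laparotomy rates, a 10-point specificity gain corresponds to anything from a 1-point to a 10-point fall in laparotomies among benign masses.

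Second, randomised women without surgery drop out of the comparison, and this can depend on arm. A reader might infer that the estimate is necessarily biased against the model, or that a true 10-point gain shrinks by nearly half. The protocol supports neither. The 5.6-point result requires every newly reclassified woman to go unoperated, a uniform 15% loss gives 10.1 points, and equal loss in both arms can overstate the gain. Neither size nor direction can be derived, because the protocol gives no benign share, baseline specificity or non-operation rate for this group.

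**What to change.** - In Task 6.2, add as the test of the stated hypothesis the proportion of all randomised women, by allocated arm, who had an exploratory laparotomy with benign histology. Women without surgery count as no.
- In Section 3, name surgical route (laparotomy, laparoscopy, none) among the outcome measures.
- Keep sensitivity and specificity as supporting measures. Report the number without histology in each arm, with a sensitivity analysis over their possible true status.
- Report malignant masses first approached as benign as the safety counterpart, and state that cancers in unoperated women are not captured without a reference standard.
- State the expected precision of the laparotomy comparison at 100 versus 200, with the baseline rate assumed.

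The cost is revised wording, at most one field in the electronic form, and keeping randomised women without surgery in the dataset. The new comparison needs no histology in unoperated women. It does not cure the low power, which has to be acknowledged or met with more women.
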